**Figure 1 figure1:**
[figure not shown]
Graphical representation of the randomized controlled trial protocol. CBT: cognitive behavioral therapy; RNT: repetitive negative thinking.

Participants will be randomly assigned, using a random-number generator, to 1 of 4 conditions: (1) intervention condition (therapist support); (2) intervention condition (no therapist support); (3) partial intervention (daily sampling and emotion valuation questions); or (4) control group (only daily sampling questions). Active control groups will be utilized to avoid artificially inflating comparisons with intervention condition outcomes [64]. The specific group allocations and the nature of other study conditions will be concealed from participants. Block/random stratification will not be used, as participants will be randomly allocated to 1 of the groups after agreeing to participate in the study. During analysis, demographic characteristics across groups will be compared, and any significant differences identified will be included as control variables.

Therapist support has been shown to improve outcomes in studies of digital mental health interventions [61]. In this study, therapist support will take the form of asynchronous written communication with a cognitive behavioral therapy (CBT) practitioner—either fully qualified or in at least their second year of training—via WhatsApp (Meta Platforms, Inc). This support will be available 2 times a week to relevant participants at specific times predetermined by the therapist. Participants will have the option to utilize this support, but will not be directed to do so. Supporting therapists will be paid at their standard hourly rate for regular patients and will receive an introduction to the app and intervention—while remaining blinded to the full aims of the study—through an online workshop conducted by members of the research team experienced in delivering rumination-focused cognitive behavioral therapy (RFCBT), before the study.

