### Participants and Power Analysis

Participants who self-report problems with RNT will be sought. The first participation in the trial is planned to commence in May 2025. As the study will be conducted remotely and recruitment will continue beyond this date, participants are expected to begin their engagement asynchronously.

To be eligible for the trial, participants must self-report problems with RNT. Participants will be excluded if (1) they are under 18 years of age at the start of the trial; (2) they are currently receiving any form of psychotherapy; or (3) they are currently receiving any form of psychiatric medication. Participants with a psychiatric diagnosis will not be excluded, provided they meet the inclusion criterion and do not meet any of the exclusion criteria listed above.

Sample size was calculated using G*Power version 3.1 [65] for a repeated-measures design with 4 independent conditions measured at 3 time points and assuming a medium effect size. This indicated a required sample size of 60 with equal randomization of participants across groups, which aligns with previous intervention studies in the field [66-68]. As our initial feasibility study during the development of the app content experienced an attrition rate of approximately 60% [69], this study aims to recruit at least double that number to mitigate the risk of significant dropout throughout the trial.

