### Statistical Analysis

#### Data Exclusion

Compliance will be defined as the completion of both the first and second weeks of the intervention content in full, along with at least 5 out of 6 exercises from weeks 3 and 4. For EMA, a compliance threshold of 80% will be used, consistent with previous research using EMIs in adult populations [90]. Additionally, the study will control for time spent within the app and the length of responses to open-ended questions.

In addition to the aforementioned compliance measures, participants who fail both attentional checks embedded within the assessments will be excluded from analyses.

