#### Analysis of Trial Outcome Data

##### Primary Outcomes

Changes in outcomes across pre-, post-, and follow-up assessments (PTQ, EBQ, PBRS, NBRS, HADS, CAQ, and BEAQ) will be analyzed using mixed-design ANOVA across all 4 conditions. Additionally, multilevel models—treating daily observations as level 1 and participants as level 2—will be used to assess associations between avoidance and mood, as well as between rumination and mood, and to examine whether these associations are moderated by condition.

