##### Secondary Outcomes

Mixed-design analysis of covariance will be conducted within the 2 intervention groups to examine whether time spent engaging with the app content serves as a covariate influencing intervention outcomes.

In-app user feedback collected through the CORTO method will be deductively coded following the process outlined by Saldana [91], using the 4 overarching categories proposed by Lukka et al [82]—(1) contextual use, (2) interaction-elicited emotional experience, (3) usability, and (4) technical issues—as a guiding framework. More detailed subdomains will be explored within each category.

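### Control variables are to be chosen by significance tests of demographics between randomised arms, and the baseline score is not entered as a covariate

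*Protocol article*

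**What the plan says.** All references are to the protocol article.

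- **Covariate rule** (Methods, Study Design, text after Figure 1): "demographic characteristics across groups will be compared, and any significant differences identified will be included as control variables".
- **Allocation** (same place): a random-number generator assigns participants to four conditions. "Block/random stratification will not be used, as participants will be randomly allocated to 1 of the groups after agreeing to participate in the study".
- **Questionnaire analysis** (Primary Outcomes): "Changes in outcomes across pre-, post-, and follow-up assessments (PTQ, EBQ, PBRS, NBRS, HADS, CAQ, and BEAQ) will be analyzed using mixed-design ANOVA", over all four conditions.
- **Daily data** (Primary Outcomes): multilevel models with days nested in participants, used "to examine whether these associations are moderated by condition".
- **Other named controls** (Data Exclusion): "the study will control for time spent within the app and the length of responses to open-ended questions". The secondary analysis of covariance, within the two intervention arms, is run "to examine whether time spent engaging with the app content serves as a covariate influencing intervention outcomes". All of these arise after randomisation.
- **Sample size** (Participants and Power Analysis): 60 in total with equal allocation, so 15 per arm, calculated "for a repeated-measures design with 4 independent conditions measured at 3 time points and assuming a medium effect size".

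No baseline questionnaire score is named anywhere as a covariate.

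**The concern.** A covariate earns its place in a randomised comparison by predicting the outcome. The stated rule asks instead whether a demographic differs significantly between arms. Among everyone randomised, the answer to that test reflects chance alone. A strongly prognostic variable is selected no more often than an irrelevant one, and with about 15 per arm a sizeable imbalance can easily miss significance.

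There are two consequences. First, the covariates in the primary model cannot be known until the data have been seen. Second, the screen considers only demographics, so it can never select the baseline PTQ, HADS or BEAQ score, although these are collected from all participants and can be expected to predict the later scores. In a trial this small, that precision is worth having.

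Because the rule is stated outright, it is not a detail that the article leaves to a fuller document.

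**Working it through.** **1. The plan's own figure.** The stated N of 60 reproduces as a group-by-time interaction test with f = 0.25, alpha 0.05, power 0.95, correlation 0.5 among repeated measures and full sphericity. None of these values is in the article, which says only that a medium effect was assumed.
- Noncentrality: f² × N × m / (1 − ρ) = 0.0625 × 60 × 3 / 0.5 = 22.5.
- Degrees of freedom: (4 − 1)(3 − 1) = 6 and (60 − 4)(3 − 1) = 112.
- Power: 0.954.

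This matters here only because it gives 60 / 4 = 15 per arm and shows that the planned test is consistent with group-by-time.

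**2. How often chance selects a covariate.** With k independent demographics tested at 0.05, the probability that at least one is selected is 1 − 0.95^k. The article gives neither k nor the test level, so both are assumed.

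| k | Probability |
|---|---|
| 3 | 14% |
| 5 | 23% |
| 10 | 40% |

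**3. What the screen does to error and power.** The first simulation used 15 per arm, four demographics unrelated to outcome, 3,000 runs per setting, and baseline-outcome correlations of 0.3, 0.5 and 0.7.
- At least one demographic was selected in about 18 to 19% of trials; 1 − 0.95⁴ = 18.5%.
- Type I error stayed between 0.041 and 0.055.
- With an assumed 0.8 SD effect in two arms and correlation 0.5, change-score power was 0.69 with or without the screen.

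The second simulation used one covariate that does predict outcome, the same effect, a post-score analysis and 8,000 runs.

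| Covariate-outcome correlation | Unadjusted | Protocol's screen | Prespecified adjustment |
|---|---|---|---|
| 0.3 | 0.72 | 0.72 | 0.75 |
| 0.5 | 0.71 | 0.72 | 0.83 |

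A repeat of the second row with another seed gave 0.70, 0.70 and 0.82. The screen recovers almost none of the available gain, because it picks the useful variable only about 5% of the time.

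**4. Baseline as a level of time versus baseline as a covariate.** Assume equal variance σ² before and after, and correlation ρ between the two scores.
- Change score: residual variance 2(1 − ρ)σ².
- Baseline as covariate: residual variance (1 − ρ²)σ².
- Ratio: (1 − ρ²) / [2(1 − ρ)] = (1 + ρ) / 2, which never exceeds 1.

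| ρ (assumed) | Covariate | Change | Ratio | Power, change | Power, covariate |
|---|---|---|---|---|---|
| 0.3 | 0.91 | 1.40 | 0.65 | 0.55 | 0.74 |
| 0.5 | 0.75 | 1.00 | 0.75 | 0.69 | 0.81 |
| 0.7 | 0.51 | 0.60 | 0.85 | 0.92 | 0.95 |

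The power columns come from the first simulation, which compares one pre score with one post score. They illustrate the size of the gain and are not the power of the planned three-time-point test.

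**The case against.** Four stronger readings are tempting, and the article does not support them.

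- **Baseline scores are not adjusted for.** This is wrong for the questionnaire analysis. The pre score is one of the three levels of time, so the group-by-time test already removes baseline differences as a change score does. What can be said is that the score is not entered as a covariate, which is less efficient.
- **The rule inflates type I error.** Simulated error stayed near 0.05 in the settings tried, so no such harm is shown.
- **Every significant difference must be chance.** That holds for everyone randomised. The comparison is made at analysis, and the article does not say on which set. Compliance and attention-check exclusions, deletion of withdrawn participants' data, and dropout (about 60% in the feasibility study) may all shrink that set, and differences within it need not be chance. This limits the argument but does not rescue the rule, since a significance screen is not a remedy for selective loss.
- **The multilevel models omit baseline covariates.** A condensed article's silence is not evidence of omission. No daily sampling before the intervention is described either, so a baseline value of the daily outcomes may not exist.

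It is also fair to object that the variance ratios do not measure the effect of the quoted sentence. They measure a separate choice, how the pre score is used, and the gain shrinks as the correlation rises: at 0.7 it is 15%, with simulated power moving only from 0.92 to 0.95. That stands, and the two costs are kept apart here.

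**Conclusion.** The point holds in a limited form. The rule makes the covariate set depend on the observed data and on imbalance rather than prognostic value. In about 14% to 40% of trials, for 3 to 10 independent demographics, chance alone would alter the model. Separately, using the pre score only as a level of time gives up precision: the covariate analysis has 0.65 to 0.85 of the change-score variance for correlations of 0.3 to 0.7. In rough sample-size terms, 60 × 0.65 = 39, 60 × 0.75 = 45 or 60 × 0.85 = 51 participants would do the work of 60.

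These figures rest on assumed numbers of demographics, an assumed 0.05 screening level, assumed correlations and equal variances, none of which the article gives. The results are not shown to be invalid. The harm is a model that is not fixed in advance and precision left unused, and the plan should be changed before analysis.

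**What to change.** 1. Delete the sentence that makes significant demographic differences into control variables.
2. For the pre, post and follow-up questionnaire outcomes, prespecify the baseline value of the same outcome as a covariate for the post and follow-up scores, or use a constrained-baseline mixed model.
3. Fix any demographic covariates in advance on expected prognostic value, for these analyses and for the multilevel models, and keep them whatever the baseline table shows. Choose only variables known to be collected: the article does not list its demographics, does not name sex as recorded, and mentions age only as an eligibility limit. Do not require a baseline daily score in the multilevel models unless one is collected.
4. Report baseline characteristics by arm descriptively, without significance tests.

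**Cost.** No new data are needed for item 2, since the baseline questionnaires are already planned for all participants. The downside is small: the questionnaire analysis would depart from the three-time-point ANOVA behind the sample size, so the text should say so. By the variance ratio above, the replacement is at least as precise.

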### Participants and Power Analysis

Participants who self-report problems with RNT will be sought. The first participation in the trial is planned to commence in May 2025. As the study will be conducted remotely and recruitment will continue beyond this date, participants are expected to begin their engagement asynchronously.

To be eligible for the trial, participants must self-report problems with RNT. Participants will be excluded if (1) they are under 18 years of age at the start of the trial; (2) they are currently receiving any form of psychotherapy; or (3) they are currently receiving any form of psychiatric medication. Participants with a psychiatric diagnosis will not be excluded, provided they meet the inclusion criterion and do not meet any of the exclusion criteria listed above.

Sample size was calculated using G*Power version 3.1 [65] for a repeated-measures design with 4 independent conditions measured at 3 time points and assuming a medium effect size. This indicated a required sample size of 60 with equal randomization of participants across groups, which aligns with previous intervention studies in the field [66-68]. As our initial feasibility study during the development of the app content experienced an attrition rate of approximately 60% [69], this study aims to recruit at least double that number to mitigate the risk of significant dropout throughout the trial.

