**Methods:**

Consenting individuals (target N=60) who meet the inclusion criteria (self-reporting problems with repetitive negative thinking) will be randomly assigned to 1 of 4 conditions: (1) intervention with therapist support and daily sampling, (2) intervention without support and with daily sampling, (3) partial intervention (emotion validation EMI only) with daily sampling, or (4) control (daily sampling only). The intervention consists of a series of modules delivered over 4 weeks, with assessments conducted before and after intervention, and again at 1-month follow-up (plus an additional 3-month follow-up for intervention participants). Data will be collected both through online self-report assessments and via the app itself. The potential of the EMI to modify the maladaptive feature of repetitive negative thinking will be assessed using mixed-design ANOVA, while the links between avoidance-mood and rumination-mood, in terms of the moderating effect of trial condition, will be evaluated using multilevel models. These will be assessed as primary outcomes. Secondary outcomes are the effects of a supporting therapist on postintervention outcomes in the intervention groups, and time spent using the app as a measure of engagement (analyzed using the mixed-design analysis of covariance). Compliance will be defined as completing both of the first 2 weeks of intervention content in full, and 5 out of the 6 exercises from weeks 3 and 4. Additionally, the study will control for both the amount of time spent in the app and the length of responses to open-ended questions.

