	**Module 3**			
		Exercise 3	Summarizing learning: identifying the context, content, consequences of users’ rumination, and how to reduce rumination and its maladaptive consequences.	

During the development process, an initial feasibility study was conducted to consult with prospective end users. Participatory workshops were held to obtain feedback on the usability and acceptability of the app content and to discuss preliminary plans for the app structure, visual layout, and features [69]. Before these workshops, participants, selected based on their rumination levels, were asked to engage with a web-based version of the proposed app content (hosted via Qualtrics; SAP SE) for 4 weeks. Participants were asked to complete a series of pre- and posttests online, designed to mimic the randomized controlled trial protocol for this trial (see the “Methods” section, except for the BEAQ measure). A series of attentional tests was also included in the online assessment to control for response reliability. To be included in the analysis, participants were required to complete the first 2 weeks of content in full, followed by 5 of the 6 exercises from weeks 3 and 4.

Of the initial 687 participants who registered interest in participating, a sample of 55 was selected through prescreening using the PTQ. Participants were selected if their overall score was 1 SD above average. Of these, 21 participants completed all measures and were included in the quantitative analysis. Four participants volunteered to engage in participatory workshops and took part in semistructured interviews with members of the research team. The semistructured interviews focused on (1) factors determining compliance and strategies to overcome challenges in following the 4-week program; (2) strong and weak aspects identified in the program content; (3) accessibility of psychoeducational content in terms of language, clarity, and length; (4) strong and weak aspects of the user experience; (5) evaluation of different exercise types; and (6) evaluation of a mock-up for apps, with users having previous experience following the 4-week program.

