## Results

Recruitment and enrollment for the trial are expected to begin in May 2025, with completion anticipated by July 2025. Data collection will conclude once the target sample size for each of the 4 conditions has been met. The main results of the trial are expected to be submitted for publication by October 2025. In addition to a formal publication in a peer-reviewed journal, the trial outcomes are anticipated to be presented in a summarized form at a relevant international conference.

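### Recruiting at least double the required 60 covers 50% attrition, not the roughly 60% cited, and the abstract and stopping rule do not settle whether 60 means randomised or analysable

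*Protocol article*

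**What the plan says.** All of this is in the protocol article.

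- **Participants and Power Analysis** describes a G*Power calculation for a "repeated-measures design with 4 independent conditions measured at 3 time points and assuming a medium effect size". The result: "This indicated a required sample size of 60 with equal randomization of participants across groups".
- The same section turns to dropout. The feasibility study "experienced an attrition rate of approximately 60% [69], this study aims to recruit at least double that number". The reason given is to mitigate the risk of dropout.
- **Development, Content, and User Evaluations** gives the counts behind that rate: "a sample of 55 was selected through prescreening using the PTQ", and "Of these, 21 participants completed all measures and were included in the quantitative analysis".
- **Abstract, Methods** puts the number differently: "Consenting individuals (target N=60) who meet the inclusion criteria" are the people who will be randomised to the four conditions. It does not mention a larger recruitment figure.
- **Results** gives the stopping rule: "Data collection will conclude once the target sample size for each of the 4 conditions has been met". The abstract's Results paragraph and Recruitment Strategy say much the same. None of them gives the number per condition or says whether it counts people randomised or people with usable data.

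**The concern.** The power section offers the doubling as its answer to the cited attrition, but the multiplier is too small for that rate. The article gives no reason to expect lower attrition in this trial, so its own planning figures do not deliver the sample size it says is required.

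The abstract adds a second problem. If 60 is the number randomised, there is no allowance for dropout at all. The stopping rule could settle the matter but is silent on what it counts. Together these places allow three different trials: 60 randomised, at least 120 randomised, or recruitment until 60 people have complete data. They differ in when recruitment stops and in how much information the primary analysis has.

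**Working it through.** **Inputs from the protocol article**

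- Required total 60, or 15 per arm (Participants and Power Analysis).
- Recruitment floor 2 × 60 = 120 (same section).
- Attrition about 60% (same section). From the feasibility counts, 55 − 21 = 34 lost and 34/55 = 61.8%, so 21/55 = 38.2% were retained.
- Abstract target: 60 consenting and randomised.

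**Step 1. Can the stated 60 be reproduced?** The article gives four groups, three time points and a medium effect. I take medium as f = 0.25, the usual convention. Alpha, power and the correlation between time points are not stated, so they are assumptions here. For the group-by-time interaction in a repeated-measures ANOVA with sphericity:

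- λ = f² × N × m / (1 − ρ), with m = 3
- df1 = (4 − 1)(3 − 1) = 6
- df2 = (N − 4)(3 − 1)

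With alpha 0.05 and N in multiples of 4, 60 is the smallest adequate total under at least three settings:

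| Target power | ρ | λ at N = 60 | Power at 60 |
|---|---|---|---|
| 0.80 | 0.25 | 0.0625 × 60 × 3 / 0.75 = 15.0 | 0.82 |
| 0.90 | 0.40 | 0.0625 × 60 × 3 / 0.60 = 18.75 | 0.91 |
| 0.95 | 0.50 | 0.0625 × 60 × 3 / 0.50 = 22.5 | 0.95 |

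So 60 is a credible output, but the article does not show which setting produced it. The test for time alone also gives 60 as the minimum at power 0.95 with ρ = 0.3.

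**Step 2. What does the recruitment floor leave?** Remaining = recruited × (1 − attrition).

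- At 60%: 120 × 0.40 = 48, or 12 per arm. The shortfall is (60 − 48)/60 = 20%.
- At 61.8%: 120 × 21/55 = 45.8, about 46.
- At 50%: 120 × 0.50 = 60. This is the highest attrition that 120 can absorb.

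**Step 3. What would leave 60?** Recruited = 60 / (1 − attrition).

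- At 60%: 60/0.40 = 150.
- At 61.8%: 60/(21/55) = 157.1, so 158.

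Rounded up to four equal arms, these are 152 and 160.

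**Step 4. What does the abstract's 60 leave?** 60 × 0.40 = 24, or 6 per arm; at 21/55, 22.9.

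**Step 5. Power at those numbers,** for the interaction test under the settings of step 1:

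| Setting (target power, ρ) | N = 60 | N = 48 | N = 24 |
|---|---|---|---|
| 0.80, 0.25 | 0.82 | 0.70 | 0.35 |
| 0.90, 0.40 | 0.91 | 0.81 | 0.43 |
| 0.95, 0.50 | 0.95 | 0.89 | 0.51 |

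**The case against.** Four points can fairly be made for the plan.

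1. **The 120 is a minimum.** The text sets a floor and speaks of mitigating dropout, not of removing its effect. That is right: 48 is what remains at the floor, not a forecast of the final sample. But no higher number appears anywhere, and the floor is the only figure that answers the cited attrition.

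2. **The 60% was not observed in this trial.** It comes from a feasibility study that used a web-based version of the content. This trial uses an app updated after user feedback, pays €50, and has two arms without the full content. Retention may well be better. Still, the protocol chose this rate for planning and does not argue for a lower one. The trial also adopts the same content-completion rule as its definition of compliance, and adds a 1-month follow-up.

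3. **The stopping rule may count completers.** If the target per condition means 15 analysable people, recruitment simply continues and no shortfall arises. This is the strongest objection. No section says it, however, and the abstract ties 60 to people who consent and are randomised.

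4. **At the floor, the loss of power may be modest.** With correlation 0.5, power is still 0.89 at 48. That is the favourable end of the range; with correlation 0.25 it is 0.70.

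A reader might go further and infer that 60 can come from only one G*Power setting, that power at 48 is therefore 0.89, or that calling the effect medium is misleading. The documents do not support these. Several settings give 60, so no single power figure can be assigned, and medium for f = 0.25 is ordinary usage. An article may also leave alpha, power and correlation to a fuller document, so their absence is not counted against the plan here.

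**Conclusion.** The concern holds in a limited form. On the article's own figures, the recruitment floor does not deliver the required sample: 120 leaves 48 at 60% attrition (about 46 at the feasibility counts), 20% short. Separately, the abstract's 60 randomised conflicts with recruiting at least 120, and the stopping rule does not resolve the conflict.

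The counts assume that feasibility attrition carries over and that recruitment stops at the floor. The power figures also assume f = 0.25, alpha 0.05, sphericity and one of the three settings shown. On that basis the consequence is moderate if 120 are recruited (power about 0.70 to 0.89) and severe if only 60 are randomised (about 0.35 to 0.51).

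A reader might infer that the trial will certainly end with 48 people. The documents do not support that: the floor may be exceeded, retention may be better, and the stopping rule may have been meant to count completers. What is established is that the stated numbers do not fit together.

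**What to change.** - State one total to be randomised and one expected analysable total. Use both consistently in the abstract (Methods and Results), Participants and Power Analysis, Recruitment Strategy, and Results.
- Say whether the target per condition in the stopping rule counts people randomised or people analysable, and give the number.
- If 120 stays the randomised total, either say that about 48 are expected to remain and give the power at that number under the G*Power settings actually used, or justify planning for attrition of 50% or less.

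This costs wording only, plus a less favourable stated figure if power is restated at 48. If the sponsor would rather keep 60 analysable at 60% attrition, the arithmetic implies about 150 randomised, which is 150 − 120 = 30 more than the floor.
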